**3) Summary**

Inpatient treatment for complicated severe acute malnutrition (SAM) continues to have a high mortality in Africa. This is partly because children are commonly brought for admission because they are seriously ill, rather than being brought to hospital because of malnutrition alone. Mortality rates are especially high where SAM is complicated by HIV or TB. The early phase of inpatient nutritional treatment for severe acute malnutrition is based on a low-protein milk known as F75, which is given to improve metabolic homeostasis prior to the re-feeding to achieve catch-up growth. F75 provides a high proportion of energy from carbohydrates, including sucrose, lactose and maltodextrin. However, malabsorption of different types of carbohydrates, but lactose in particular, is known to occur in SAM and may lead to osmotic diarrhoea. Diarrhoea is common in children with SAM and is associated with increased mortality. Furthermore, switching from a catabolic state to a high energy diet that consists of predominantly carbohydrates can lead to ‘re-feeding syndrome’ that may lead to severe electrolyte abnormalities and multiple organ dysfunction.

The aim of this trial is to determine whether reducing the carbohydrate content of F75, and removing lactose, improves the stabilisation of severely malnourished children. The trial will involve randomising children who are eligible to receive F75 milk to either the current formulation or a revised formulation. Both formulations will be given according to current recommendations regarding frequency of feeding and caloric value. Since the purpose of F75 is to stabilise the child metabolically and biochemically, the primary endpoint of the trial will be time to stabilisation (the end of the first phase of treatment for severe acute malnutrition). Blood and stool samples at admission and after three days will be used to determine the effects on carbohydrate and fat malabsorption and evidence of the re-feeding syndrome. Children will be followed up until discharge from hospital. The project has been planned in consultation with the World Health Organisation (WHO) and, if the revised formulation of F75 results in improved outcomes, will lead to a global change in recommendations for its formulation.

**4) Introduction**

Admission to hospital with complicated severe acute malnutrition (SAM) in Africa commonly has a case fatality of 10-30%.[^1-3^](#_ENREF_1) Importantly, children are usually admitted to hospital because they are severely ill rather than for malnutrition alone. Mortality may be improved to some extent by adherence to WHO recommended management,[^1^](#_ENREF_1)^,^[^2^](#_ENREF_2) but the direct application of these guidelines to all contexts is controversial.[^4^](#_ENREF_4) The WHO guidelines were designed on the basis of historical data on nutrient requirements and medical treatments and almost none of the recommendations are supported by evidence from clinical trials.

For the treatment of complicated inpatient SAM, the guidelines consist of three distinct phases of treatment:[^5^](#_ENREF_5) phase 1 or stabilization phase where a low protein, liquid diet (F75) is introduced with a reduced energy intake (80-100 kcal/kg/day). Once a child has stabilised, there is a ‘transition phase’ consisting of either ready to use therapeutic foods (RUTF) with supplemental F75 or alternatively another milk formula known as F100. RUTF is a peanut based, energy dense supplement used to obtain catch-up growth. F100 is a liquid formula with a higher energy density and protein content than F75. The caloric intake is increased daily to a maximum of 130 kcal/kg/day. Finally, ‘Phase 3’ is the recovery phase during which the aim is to achieve catch-up growth with either RUTF or F100.

Typically, the highest mortality rate is found in the early phases of treatment. Children who fail treatment early often have profuse diarrhoea, signs of circulatory insufficiency which is hard to treat. The most recent reports from Zambia and Kenya note a prevalence of diarrhoea of more than 60% amongst children with SAM and it is associated with increased mortality.[^6^](#_ENREF_6)^,^[^7^](#_ENREF_7) Currently at Kilifi County Hospital and Coast Provincial General Hospital, ~20% of children are given either a diluted or lactose-free milk feed during rehabilitation of SAM (unpublished data), although there are no specific guidelines for this. Diarrhoea may be caused by a viral or bacterial gastroenteritis, sepsis, or may be nutritionally induced (osmotic). There are no routinely available tests to distinguish osmotic from infective or other causes of diarrhoea in hospitals in sub-Saharan Africa. Rotavirus vaccine will be introduced in 2014 and its contribution to diarrhoea amongst children with SAM is unknown.

The proportion of energy derived from carbohydrates in F75 is high. The carbohydrates in F75 milk (as well as F100 and RUTF) consist of a mixture of maltodextrin, sucrose and lactose. Disaccharides such as maltose, lactose or sucrose are normally hydrolysed into monosaccharides by disaccharidases localized at the tip of small intestinal villi. The monosaccharides such as glucose and galactose can then be transported across the apical membrane through Na^+^ dependent glucose transporter, whilst fructose makes use of a facilitative fructose transporter. There is limited information on the intestinal function and intestinal carbohydrate absorption in malnourished children. However, data from Jamaica and South Africa suggest that there is impaired absorption of disaccharides (lactose and sucrose), regardless of the presence or suspicion of gastroenteritis.[^8^](#_ENREF_8)^,^[^9^](#_ENREF_9) Limited histological evidence has shown intestinal atrophy in children with SAM.[^10-12^](#_ENREF_10) These data are consistent with clinical signs of lactose malabsorption found in children with severe malnutrition.[^13^](#_ENREF_13) Recently, evidence of impaired absorption of monosaccharide glucose in children with SAM was reported in Malawi.[^14^](#_ENREF_14)

Apart from diarrhoea, early deterioration may also be related to severe metabolic derangements due to a sudden change from a catabolic to an anabolic state, resulting in refeeding syndrome.[^15^](#_ENREF_15) Refeeding syndrome is characterized by hypophosphataemia, hypokalaemia, hypomagnesaemia and sodium retention. These severe electrolyte disturbances can lead to impaired cardiac, pulmonary and neurological function and are often hard to treat. By receiving energy predominantly from sugars, pancreatic insulin secretion is increased which induces uptake of electrolytes including phosphate and potassium, into cells. Furthermore, as protein synthesis is stimulated, increased production of adenosine tri-phosphate (ATP) leads to a higher cellular demand for phosphate.[^15^](#_ENREF_15) Although insulin secretion appears to be partially impaired in the early stages of refeeding, hypophosphatemia is a common feature during refeeding of malnourished children, and is associated with mortality.[^16-18^](#_ENREF_16)

In this trial, we aim to evaluate the outcome of using a revised formulation of F75 milk with reduced carbohydrate composition and without lactose, compared to the current formulation of F75 during the initial stabilisation period amongst children with severe acute malnutrition. In the new formulation, more will be provided by lipids and the total energy provided will be unchanged. The trial will be undertaken in two hospitals in Kenya and one hospital in Malawi.

**5) Justification**

There are theoretical reasons why carbohydrates in F75 might be associated with the development of diarrhoea and refeeding syndrome in severely malnourished children. However, there are no data from trials to inform the optimal carbohydrate content in therapeutic diets for malnourished children. This trial has the potential to improve treatment guidelines, and thereby the outcomes of malnourished children. Amongst children with SAM who present with, or develop diarrhoea after admission, it is unknown what proportion are due to infective and non-infective causes.

## 6) Null Hypothesis

## Reducing carbohydrates in F75 milk has no effect on the rate of stabilisation amongst children with SAM admitted to hospital.

## 7) Objectives

**General objective:**

- To optimise re-feeding diet for severely malnourished children to achieve highest recovery rate and lowest rate of complications.

**Specific objectives:**

- To determine the efficacy on time to stabilisation of a formulation of F75 milk with reduced carbohydrate content compared to the current standard formulation of F75 amongst hospitalised children with SAM.
- To determine the frequency of the biochemical abnormalities associated with re-feeding syndrome, osmotic and infective diarrhoea amongst hospitalised children with SAM.

**8) Design**

The trial is designed as a multicentre randomized double-blind intervention trial. The trial will examine the time to reach the transition phase amongst children with severe acute malnutrition receiving F75 milk with the current standard carbohydrate content and those receiving a modified formulation of F75 with reduced carbohydrate content without any lactose. The total energy, protein and micronutrient content of the two formulations will be the same. All other aspects of care will be the same in both arms, and be provided according to the Kenyan National Guidelines for the Integrated Management of Acute Malnutrition.[^20^](#_ENREF_20)

***a) Study Sites***

### Paediatric wards of Kilifi County Hospital and Coast Provincial General Hospital, Kenya and Queen Elizabeth Hospital, Blantyre, Malawi.

### ***b) Study population***

***Inclusion Criteria:***

- Age 6 months to 13 years.
- Severe malnutrition defined as: mid upper arm circumference (MUAC) <11.5cm if less than 5 years old;[^19^](#_ENREF_19) or weight for height Z score <-3; or kwashiorkor as defined in the current Kenyan and WHO guidelines.[^20^](#_ENREF_20)
- Admitted to hospital because of medical complications as defined in the current WHO guidelines or fails an appetite test if there are no complications.[^20^](#_ENREF_20)
- Eligible to start F75 milk by current Kenyan and WHO guidelines.[^20^](#_ENREF_20)

***Exclusion Criteria:***

- Declined to give informed consent
- Known allergy to milk products
- Any other reason the consenting investigator thinks that in the child’s best interests it inappropriate for them to take part.

***c) Sampling***

Children admitted with severe malnutrition, defined by anthropometry according to WHO guidelines, will be recruited at CPGH, Mombasa, Kilifi County Hospital and Queen Elizabeth Central Hospital (QECH), Blantyre, Malawi.

*Sample size calculation*

Based on clinical data from the actual sites, we have observed that around 50% of patients to have transitioned to the second phase of treatment by day 5. We aim for a 10% absolute increase in percentage transitioned at day 5 to 60%, which gives a hazard ratio of 1.35. Sample size for survival time was calculated using the *stpower* command in Stata version 12. Using α=0.05, 80% power, the number of patients required to demonstrate a hazard ratio of 1.35 is 381 per arm. We will aim at 420 per arm to allow for contingencies. It is anticipated that 400 children will be enrolled at CPGH, 120 at KCH and 320 at QECH. However, these figures will be adjusted in line with actual recruitment.

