### (b) Data management/analysis

The trial will use the GCP-compliant Openclinica (<https://openclinica.com/> ) database system, which will be hosted at KWTRP in Kenya. Originally developed for small oncology trials, this system has become the leading open-source clinical data capture system for clinical trials. It allows secure remote data entry online from the sites, provides a real-time reporting system and flagging of inconsistencies and database changes for monitoring. We have used this system for several large clinical trials, which have been programed and maintained by the data manager who will be working on this trial. The trial will be register on clinicaltrials.gov along with pre-specified endpoints. Data cleaning and record verification will be completed and a written analysis plan agreed before the database is un-blinded.

Descriptive statistics on baseline characteristics of the participants in each arm will be provided. Bias will be determined by maintaining a screening log of all potentially eligible participants and those who were excluded or randomized into the two arms. This will be presented as a flow diagram in the final published report according to CONSORT statement guidelines.

The primary outcome will be assessed using a Kaplan-Meier analysis and Cox proportional hazards analysis comparing the rate of stabilisation between arms. Differences between arms in the number of days to stabilisation will be compared using a two tailed Mann-Whitney *U* test. Children who die prior to stabilisation will be included in the primary analysis as ‘not stabilised’. Secondary endpoints with binary outcomes (e.g. overall mortality) will be analysed using contingency tables and a chi squared test. Where adjustment for baseline parameters is required, relative risks will be calculated. For continuous variables and count data (e.g. days receiving rehydration fluids or days with diarrhoea), a suitable general linear model (e.g. linear regression, Poisson regression) will be used. For time to discharge, Kaplan-Meier and Cox proportional hazards analysis will be used. These analyses are conducted on the intention-to-treat principle and are considered the confirmatory analysis. We will conduct tests of heterogeneity of effect, and effect modification for both kwashiorkor and HIV infection, which are considered, *a priori,* to potentially alter the response to F75.

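### The stated hazard ratio of 1.35 does not follow from 50% versus 60% transitioned at day 5 (that gives 1.32), and 381 per arm does not follow from 1.35; the stated power still holds

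*Protocol*

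**What the plan says.** The protocol, section 8 (Design), c) Sampling, starts from site data showing "around 50% of patients to have transitioned to the second phase of treatment by day 5". It then states the target: "We aim for a 10% absolute increase in percentage transitioned at day 5 to 60%, which gives a hazard ratio of 1.35". The method is given only as a survival-time calculation with Stata's stpower command, and the result is: "Using α=0.05, 80% power, the number of patients required to demonstrate a hazard ratio of 1.35 is 381 per arm". The planned number is then raised to 420 per arm for contingencies. The sub-command, the event probability, the number of events and the sidedness of the test are not given.

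Under Outcome measures in d) Procedures, the primary outcome is stabilisation, meaning entry to the transition phase, and children who die first count as not transitioned. Section 9 (b), Data management/analysis, plans Kaplan-Meier and Cox proportional hazards analyses of the rate of stabilisation.

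**The concern.** The paragraph makes a chain of two claims: the proportions give the hazard ratio, and the hazard ratio gives the sample size. Since the event is transition, the survival function is the share not yet transitioned, and benefit means a hazard ratio above 1. Read this way, neither link holds.

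This matters because 1.35 is the only effect size the protocol states on the scale of its primary Cox analysis. Readers are likely to set the estimate and its confidence interval against it. As written, nobody can reproduce the paragraph from its own inputs.

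**Working it through.** **Inputs**
- Control: 50% transitioned by day 5, so untransitioned share S1 = 0.50 (c) Sampling).
- Target: 60% transitioned by day 5, so S2 = 0.40 (c) Sampling).
- Level 0.05 and power 80% (c) Sampling). Two-sided is assumed. The paragraph does not say, but the companion test on days to stabilisation "will be compared using a two tailed Mann-Whitney" U test. A one-sided level with a ratio of 1.35 and 55% events would need about 250 per arm, which does not fit.
- Equal arms, as implied by the equal numbers per arm.
- k = (1.960 + 0.842)² = 7.849.

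**Formulas**
- Hazard ratio under proportional hazards: HR = ln(S2)/ln(S1).
- Freedman log-rank events: k × ((1 + HR)/(1 − HR))².
- Schoenfeld events: 4k/(ln HR)².
- Total children = events / mean event share; per arm = half of that, rounded up.

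**1. Reproducing 381.** Use 0.50 and 0.60 as untransitioned shares, which means transition falling from 50% to 40%.
- HR = ln(0.60)/ln(0.50) = 0.737; its inverse is 1.357.
- Freedman events = 7.849 × (1.737/0.263)² = 342.3.
- Mean event share = (0.50 + 0.40)/2 = 0.45. Unrounded events / 0.45 = 760.6, so 380.3, rounded up to **381 per arm**. Schoenfeld gives 375.

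**2. The stated direction, 50% to 60%.**
- HR = ln(0.40)/ln(0.50) = **1.322**.
- Freedman events = 7.849 × (2.322/0.322)² = 408.3, so 409.
- Mean event share = (0.50 + 0.60)/2 = 0.55. 408.3/0.55 = 742.4, so **372 per arm**. Schoenfeld gives 367.

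**3. A hazard ratio of 1.35 taken literally.**
- Transitioned at day 5 = 1 − 0.50^1.35 = **60.8%**.
- Freedman events = 7.849 × (2.35/0.35)² = 353.8. Mean event share = (0.50 + 0.608)/2 = 0.554. Total 638.9, so **320 per arm**.
- Schoenfeld events 348.6, total 629.4, so **315 per arm**.
- With the event share held at 0.55 the figures are 322 and 317.

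**4. Other routes to 381.** A ratio of 1.35 with a 45% event share gives 394 (Freedman) or 388 (Schoenfeld). A comparison of two proportions, 50% against 60%, gives 388, or 408 with continuity correction. None of these gives 381.

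**5. Power for 50% versus 60% (HR 1.322), counting events to day 5.**

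| Per arm | Events (55%) | Freedman | Schoenfeld |
|---|---|---|---|
| 381 | 762 × 0.55 = 419.1 | 81.0% | 81.5% |
| 420 | 840 × 0.55 = 462 | 84.6% | 85.1% |

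**6. Optional context: follow-up to discharge.** The protocol gives no final stabilised share. If 70% to 90% stabilise before discharge (assumption), 420 per arm yields 588 to 756 events. Schoenfeld power for HR 1.322 is then about 92% to 97%.

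**The case against.** The strongest reply is that nothing of substance is wrong. The target is stated in absolute terms and in the right direction, and the control rate is itself only approximate. A ratio of 1.35 instead of 1.32 moves the implied day-5 share from 60% to only 60.8%. The correct requirement of 372 is 2.4% below 381. This stands, and it limits the point to a correction of stated figures.

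The documents do not support three stronger readings.

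- *The power is wrong or the trial is too small.* For the stated target, 381 per arm meets the stated 80%, and 420 exceeds it.
- *The calculation was certainly run backwards.* The protocol shows none of the stpower inputs. The reversed run gives an inverse of 1.357, which rounds to 1.36 and becomes 1.35 only by truncation. Another route also reaches 381: the literal ratio of 1.35 needs 319.4 per arm before rounding, and an assumed 16% loss gives 319.4/0.84 = 380.3, so 381. The protocol states no such loss and adds its contingency separately, so this route is less plausible, but it shows that the origin is not uniquely identified.
- *The interim look uses a wrong benchmark.* The protocol states no event count. The look is triggered when half the participants are recruited and is guided by Haybittle-Peto criteria, so it depends on neither an event total nor the ratio of 1.35.

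Sizing on a day-5 landmark while following children to discharge can also be defended as conservative. The primary analysis paragraph sets no time horizon, and power over later horizons may properly be left to the analysis plan.

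**Conclusion.** The sample size paragraph is internally inconsistent in two places. A rise from 50% to 60% corresponds to a hazard ratio of 1.32, not 1.35. A ratio of 1.35 would need about 315 to 320 per arm, not 381. Both statements rest on proportional hazards, and the second also on a two-sided 5% level and 1:1 allocation. A reversed entry of the proportions is the likeliest source, since it matches 381 exactly, but it remains an inference, and the inconsistency stands without it.

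The error runs in the safe direction: it asks for 381 where 372 would do. The absolute target, the planned recruitment and the claim of 80% power all survive. The reason to act is that the effect size on the scale of the primary analysis is misstated and the derivation cannot be reproduced. It is a correction to make, and it does not threaten the trial.

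**What to change.** Keep 420 per arm and restate the paragraph along these lines: 50% to 60% transitioned at day 5 corresponds to a hazard ratio of 1.32; about 409 events and 372 children per arm give 80% power (Freedman log-rank, two-sided 5% level, 55% mean event share); 420 per arm gives about 85% power on events to day 5. Name the stpower sub-command used, and confirm from the saved Stata command, if it exists, how the proportions were entered.

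Optionally, add one sentence saying that a Cox analysis to discharge would have about 92% to 97% power for a hazard ratio of 1.32 at 420 per arm, if 70% to 90% of children stabilise before discharge, with that range labelled as an assumption.

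The cost is the rewording of one paragraph. Recruitment, the primary analysis and the interim rule do not change.

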Children will be examined daily whilst in hospital and clinical status recorded on a standardised proforma (appendix d). A blood sample and stool sample will be taken at day 3 to assess for metabolic effects of refeeding and carbohydrate malabsorption. If children deteriorate during the transition phase or phase 2 and are placed back on phase 1, they will receive the same F75 intervention diet as allocated during the initial treatment. The decision to discharge will be made by the usual clinical team rather than trial personnel. Food supplements and/or nutritional counselling and follow up in the nutritional clinic that are the current standard of care at each institution will also be done at discharge. No study follow up after discharge will be done.

[figure not shown]

*Outcome measures*

*Primary outcome:* the choice of primary outcome is based on the therapeutic purpose of F75, which is to achieve stabilisation and thereby allow a child to progress to feeds with higher protein and energy content to enable catch-up growth.

The primary outcome is stabilisation, defined as having reached the second (transition) phase of treatment. The criteria for stabilisation will be according to WHO guidelines:

Absence of any WHO danger or emergency signs: obstructed breathing, respiratory distress, cyanosis, shock (delayed capillary refill plus fast & weak pulse plus temperature gradient), severe anaemia (Hb<5g/dl), congestive cardiac failure, impaired consciousness, convulsions, severe dehydration, profuse watery diarrhoea, vomits everything, hypothermia.

*and*

If there is oedema at baseline, loss of oedema defined as improving from a severe +++ oedema (severe: generalized bilateral pitting oedema including feet, legs, arms and face) to ++ oedema (moderate: no upper arm or upper leg oedema and no facial oedema or from ++ oedema to + (mild: only feet/ankle oedema) or none;

*and*

Tolerating full prescribed volume of F75 feeds and observed to be completing the feeds.

For analysis, children who die before stabilisation will be classified as ‘not transitioned’.

*Pre-specified secondary outcomes*:

1. Number days with diarrhoea (3 or more loose stools within 24h);
2. Number days requiring rehydration fluids (ReSoMal or IV fluids);
3. Percentage change in weight between admission and day 5;
4. Changes in sodium, potassium, magnesium, calcium, phosphate and albumin between admission and day 3;
5. Faecal electrolytes, pH and fat at day 3;

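### The stated hazard ratio of 1.35 does not follow from 50% to 60% transitioned by day 5 (that gives 1.32), and 381 per arm fits neither figure

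*Protocol*

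**What the plan says.** The calculation is in the Protocol, section 8) Design, c) Sampling. The control figure comes from the sites' own data: "we have observed that around 50% of patients to have transitioned to the second phase of treatment by day 5". The target and effect size follow: "We aim for a 10% absolute increase in percentage transitioned at day 5 to 60%, which gives a hazard ratio of 1.35". On method the paragraph says only "Sample size for survival time was calculated using the *stpower* command in Stata version 12", and the result is "Using α=0.05, 80% power, the number of patients required to demonstrate a hazard ratio of 1.35 is 381 per arm". Enrolment is then rounded up: "We will aim at 420 per arm to allow for contingencies".

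The event is defined under Outcome measures in d) Procedures: "The primary outcome is stabilisation, defined as having reached the second (transition) phase of treatment". Children who die before stabilising count as not transitioned. Section 9) Data, (b) Data management/analysis, compares the rate of stabilisation by Kaplan-Meier and Cox proportional hazards methods.

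**The concern.** In a time-to-event calculation, survival means not yet having had the event. Here the event is the good outcome, so a child who survives in that sense is one who has not yet transitioned. A 50% versus 60% transition rate is therefore 50% versus 40% event-free, and the hazard ratio must be computed from those two figures. The stated 1.35 looks instead like the ratio for 50% versus 60% event-free, which describes 50% versus 40% transitioned.

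This paragraph is where the Protocol fixes the primary effect size. If its four figures (50%, 60%, 1.35 and 381) do not fit together, a reader cannot tell which effect the trial was sized for. Anyone who tries to reproduce the published calculation from its stated inputs will also fail.

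**Working it through.** **Inputs.** From c) Sampling: control 50% and target 60% transitioned by day 5, α = 0.05, 80% power, 381 per arm, 420 per arm enrolled. Assumed, because not stated: two-sided test, Freedman log-rank formula, 1:1 allocation, events counted to day 5 only.

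**Formulas.**
- Hazard ratio under proportional hazards: HR = ln(S_new)/ln(S_control), where S is the proportion still event-free at day 5.
- Events (Freedman): E = (1.960 + 0.842)² × [(HR + 1)/(HR − 1)]², where the first factor is 7.849.
- Number per arm: E / (2 × mean event probability).
- Power: Φ(√E × (HR − 1)/(HR + 1) − 1.960).

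**1. Reproducing 381.** Take 0.50 and 0.60 as event-free proportions.
- The ratio is ln(0.50)/ln(0.60) = 1.357 (inverse 0.737).
- E = 7.849 × (2.357/0.357)² = 342.3.
- Mean event probability = 1 − (0.50 + 0.60)/2 = 0.45.
- Total = 342.3/0.45 = 760.6, or 380.3 per arm, which rounds up to 381.

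**2. The stated proportions, with transition as the event.** The event-free proportions are 0.50 and 0.40.
- HR = ln(0.40)/ln(0.50) = 1.322.
- E = 7.849 × (2.322/0.322)² = 408.3, so 409 events.
- Mean event probability = 0.55.
- 408.3/(2 × 0.55) = 371.2, so 372 per arm.

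**3. The stated hazard ratio with the stated control rate.**
- The event-free proportion in the new arm is 0.50^1.35 = 0.392, so 60.8% transitioned.
- E = 7.849 × (2.35/0.35)² = 353.8.
- Mean event probability = 1 − (0.50 + 0.392)/2 = 0.554.
- 353.8/(2 × 0.554) = 319.4, so 320 per arm.

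**4. Power on the same day-5 basis.**

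| Per arm | HR | Events | Power |
| --- | --- | --- | --- |
| 381 | 1.322 | 762 × 0.55 = 419 | 81% |
| 381 | 1.35 | 762 × 0.554 = 422 | 86% |
| 420 | 1.322 | 840 × 0.55 = 462 | 85% |

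**5. Other routes to 381.**
- Schoenfeld's formula gives 375 per arm for case 1, 367 for case 2 and 315 for case 3.
- A two-proportion test of 50% versus 60% gives 388, or 408 with continuity correction.
- At HR 1.35 with 55% events, a one-sided test gives 254 per arm and 90% power gives 425 to 431.

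None of these gives 381.

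**The case against.** **The control rate is only approximate.** The text says around 50%. A control rate of 49.3% with a 60% target does give 1.35, since ln(0.40)/ln(0.507) = 1.35. So 1.35 taken alone is close to the precision of its input. That much stands. But this reading gives up the exact 10-point increase that the same sentence states, and it does not produce 381.

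**Deaths might explain 1.35.** If deaths are treated as a competing event, a cause-specific hazard ratio of about 1.35 can arise. It takes roughly 20% control deaths by day 5 (an assumption, with constant hazards and equal death hazards in both arms). That reading sits badly with counting deaths as not transitioned. At 55% transitions it also needs only about 317 to 322 per arm.

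**The cause is not proved.** The Protocol gives neither the subcommand nor the command line, and 1.357 rounds to 1.36 rather than 1.35. This stands: the reversed input is a probable explanation, supported by the exact match to 381. The gap between 1.32 and 1.35 does not depend on it.

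**The powers are conditional.** Children are followed daily until discharge, and the primary analysis is not limited to day 5. The powers above therefore describe an assumed cut-off, not the trial's full power. This also stands.

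**Interim decisions.** A reader might infer that the wrong hazard ratio would mislead the monitoring committee through a conditional-power or futility rule. The Protocol contains no such rule: it has one interim analysis, guided by the Haybittle-Peto criteria. Nor does it make 1.35 a threshold for success.

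**Conclusion.** The concern holds as an error in the stated effect size and its justification. With transition as the event, 50% to 60% is a hazard ratio of 1.32, and 1.35 corresponds to 60.8%. The figure of 381 per arm belongs to a different input, most likely the transition percentages read as event-free proportions.

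A reader might infer that the trial is underpowered. The figures do not support that. The reversed reading has too large a hazard ratio (1.357 instead of 1.322) and too low an event probability (0.45 instead of 0.55), and the two nearly cancel. The corrected requirement of 372 lies below 381, and the planned 420 keeps about 85% power for the stated 10-point aim.

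The hazard ratio rests only on proportional hazards and the stated proportions. The sample sizes and powers also rest on the Freedman formula, a two-sided test and events counted to day 5.

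**What to change.** In c) Sampling, restate the hazard ratio as 1.32 for 50% to 60% transitioned by day 5. Replace 381 with the recomputed requirement, about 372 per arm (409 events) on the day-5 log-rank basis. Name the formula, the sidedness and the period over which events are counted. The sponsor should check the original *stpower* command, which would settle how the percentages were entered. Keep the enrolment target of 420 per arm.

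The cost is a correction to the text. Enrolment and trial conduct do not change.
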